#### 2.4.3. Randomization and Blinding

Eligible patients in each RCT will be equally randomized to receive either HXZQ oral liquid or placebo through an interactive web response system. A center-stratified random sequence will be created with SAS 9.2 (SAS Institute Inc., Cary, USA). The randomization will be independently performed and managed by the Institute of Basic Research in Clinical Medicine (IBRCM), China Academy of Chinese Medical Sciences (Beijing, China). Patients and researchers involved in the trial including clinicians, research assistants, outcome assessors, and statisticians will be blinded to treatment allocation. In the observational study part, patients will receive no experimental interventions of this study. Investigators will just document the medical records, and blinding is not required.

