### 2.5. Outcome Measurements

#### 2.5.1. Primary Outcome

For all AD patients, the primary outcome is the change in the Eczema Area and Severity Index (EASI) scores from baseline to the end of treatment (4^th^ week). EASI is the core outcome measurement instrument for AD, and the higher the score is, the more severe the AD is [29]. For IBS-D patients, the proportion of responders for adequate relief (AR) is the primary outcome evaluating the degree of symptom alleviation [30]. Throughout the study, IBS-D patients will be weekly asked the question: “Has your irritable bowel syndrome pain and discomfort adequately relieved in the past week?” (yes/no). Responders are defined as those who answer “yes” for at least 50% of the time, for example, in the RCT, that is, 2 out of 4 weeks in the treatment period. The proportion will be separately analyzed in the treatment period and the follow-up period.

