### 2.8. Statistical Analysis

#### 2.8.1. Sample Size Calculation

Sample size calculation of this trial consists of two parts: the RCTs and the observational study. Firstly, the sample size of each RCT was estimated, and the detailed estimation process can be found in subtrial protocols [25, 26]. In brief, a total of 430 patients diagnosed with dampness pattern (218 AD patients and 212 IBS-D patients) will be enrolled in the RCTs. Secondly, we assumed that the prevalence of dampness pattern is 39% in the AD population and is 81% within the IBS-D based on previous studies [33, 34]. Thus, 560 patients are required for the AD cohort and 270 for the IBS-D cohort. Considering a 15% loss to follow-up rate, the total sample size of cohorts is adjusted to 1000. Therefore, 570 patients diagnosed with nondampness pattern are required in the observational studies (as shown in Table 1).

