#### 2.8.2. Statistical Methods

A statistical analysis plan (SAP) will be developed prior to the completion of the trial. All data will be analyzed by statisticians using SPSS 18.0 (IBM SPSS Inc., Armonk, New York, USA) and SAS 9.2 (SAS Institute Inc., Cary, USA), and two-sided *P* values <0.05 are considered statistically significant.

First, the analysis will be undertaken independently for each RCT [25, 26]. Baseline characteristics will be summarized using descriptive statistics and will be listed by groups. Efficacy analysis will be performed in both intention-to-treat (ITT) and per-protocol (PP) populations. Missing data will be processed with the multiple imputation method, and if necessary, sensitivity analysis will be used to explore the robustness of the results. For all outcomes, *t*-test or Mann–Whitney *U* test will be employed for continuous variables; Chi-squared test or Fisher's exact test will be used for categorical variables. The changes across time among outcomes will be analyzed by repeated measure analysis of variance. Center effect and other factors based on professional judgement like gender, age, and disease course will be adjusted by logistic regression model or Cox regression model. For safety assessments, comparisons of the incidence and severity of AEs or adverse drug reactions (ADRs) between the groups will be performed by Chi-square test, Fisher's exact test, or Wilcoxon rank-sum tests based on the data characteristics. Occurrences of AEs will be listed in a summary table containing the time of occurrence, severity, duration, adopted measures, causality assessment, and prognosis.

Second, the analysis of the observational study will be conducted for each of the two disease (AD and IBS-D) populations. To investigate the real-world based effectiveness in this part, some exploratory analysis methods will be adopted [35]. Briefly, baseline characteristics of these nondampness pattern patients will be described using univariate analysis to profile the general demographics, disease features, and medication uses for each disease group. Then, all outcomes will be analyzed and compared between different medication groups by propensity score matching (PSM). Safety assessments of observational part will follow the same procedures and methods as those in the RCTs.

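### The only adjusted models named for the RCTs (logistic and Cox) cannot be fitted to the CHARM primary outcome, a continuous EASI change, so its main test is unadjusted and its stated centre adjustment is unworkable

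*Protocol article*

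**What the plan says.** Section 2.5.1 of the protocol article states that for AD patients "the primary outcome is the change in the Eczema Area and Severity Index (EASI) scores from baseline to the end of treatment", at week 4. For IBS-D the primary outcome is binary: adequate-relief responder or not.

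Section 2.8.2 gives the RCT methods, at a two-sided level where P "values <0.05 are considered statistically significant":

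- **Group comparison, all outcomes:** a t-test or Mann–Whitney U "test will be employed for continuous variables; Chi-squared test or Fisher's exact test will be used for categorical variables". No covariate or centre term is attached.
- **Course over time:** "The changes across time among outcomes will be analyzed by repeated measure analysis of variance". Again no centre or covariate term is stated.
- **Adjustment:** centre effect and other factors, chosen on professional judgement, "like gender, age, and disease course will be adjusted by logistic regression model or Cox regression model".

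Section 2.4.3 makes centre the stratification factor: "A center-stratified random sequence will be created with SAS 9.2". Table 3 schedules EASI at weeks 0, 2, 4 and 8 in the AD trial, so baseline EASI is available. Mixed-effects and multilevel models appear only later in section 2.8.2, for changes in CM pattern.

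**The concern.** The adjustment sentence covers the RCT outcomes generally, but the two models it names suit only binary and time-to-event data. For the CHARM primary outcome there is then a main test that ignores the stratification factor and baseline EASI, and an adjusted analysis that cannot be carried out.

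Two things are at stake.

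- **Precision.** A change score remains correlated with baseline. Without baseline as a covariate, some explainable variation stays in the error term, and a chance baseline difference between arms is not fully corrected.
- **Pre-specification.** An adjusted EASI result would have to be improvised. The obvious way to make logistic regression usable is to dichotomise EASI, which replaces the primary outcome with something close to the secondary outcomes EASI-50 and EASI-75.

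**Working it through.** **1. Match each model to the outcomes in section 2.5.**

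| Outcome | Type | Logistic | Cox |
|---|---|---|---|
| EASI change (CHARM primary) | continuous | no | no |
| Pruritus NRS, BSA, Skindex-29, EQ-5D-5L, IBS-SSS, IBS-QOL | score or continuous | no | no |
| EASI-50, EASI-75 | binary | yes | no |
| Adequate-relief response (CHAIRS primary) | binary | yes | no |

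No outcome is defined as a time to event, so Cox regression has nothing to act on in the RCTs as described.

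**2. The plan's own figure.** The RCT sizes are "218 AD patients and 212 IBS-D patients". The 218 cannot be reproduced, because the effect size, SD and power for EASI change are left to the CHARM protocol, which is not shown. What can be said is that 109 per arm (1:1), two-sided alpha 0.05, detects (1.960 + 0.842) × √(2/109) = 0.379 SD of change with 80% power.

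**3. Precision lost by leaving out baseline.** Let rho be the baseline-to-week-4 correlation and assume equal SDs, σ.

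- Variance of change: 2(1 − rho)σ²
- Residual variance with baseline as covariate: (1 − rho²)σ²
- Ratio r = (1 − rho²) / [2(1 − rho)] = (1 + rho)/2

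Assume the unadjusted test has 80% power at N = 218. ANCOVA power is then Φ(2.802/√r − 1.960), and the N giving ANCOVA 80% power is 218 × r, rounded up.

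| rho (assumed) | r | ANCOVA power | N for 80% |
|---|---|---|---|
| 0.3 | 0.65 | 93.5% | 142 |
| 0.5 | 0.75 | 89.9% | 164 |
| 0.7 | 0.85 | 86.0% | 186 |
| 0.9 | 0.95 | 82.0% | 208 |

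**4. Sensitivity to the equal-SD assumption.** With week-4 SD equal to k times baseline SD, r = (1 − rho²)k² / (1 + k² − 2·rho·k). Both values of k below are illustrative.

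- k = 1.3: r = 0.75 × 1.69 / 1.39 = 0.91 at rho 0.5, and 0.51 × 1.69 / 0.87 = 0.99 at rho 0.7. The gain nearly vanishes.
- k = 0.8: r = 0.75 × 0.64 / 0.84 = 0.57 at rho 0.5, and 0.51 × 0.64 / 0.52 = 0.63 at rho 0.7. The gain is larger than in step 3.

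**5. Effect of ignoring centre.** If a share s of the variance of change lies between centres and arms are balanced within centre, the unadjusted standard error is too large. The true two-sided error rate is about 2[1 − Φ(1.960/√(1 − s))], which is 0.044 at s = 0.05 and 0.039 at s = 0.10.

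**6. Simulation of both together.** Each setting had 2,000 trials of 218 patients, with rho 0.5 or 0.7, 7 centres and centre share 0 to 10% (all assumed). Power was 0.76 to 0.80 for the t-test on change and 0.84 to 0.90 for the linear model with baseline and centre. Type I error was 0.033 to 0.054 and 0.045 to 0.053 respectively.

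**The case against.** The case for leaving the text alone has real substance.

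- **The adjustment works for part of the plan.** A reader might infer that centre adjustment is impossible in both trials. It is not: logistic regression with centre suits adequate-relief response and EASI-50/75. The defect is confined to continuous outcomes. This stands.
- **Repeated-measures ANOVA is also named.** It is a linear model that could use the baseline measurement and carry a centre factor. That is fair, but the text gives it neither a centre nor a covariate term and sends adjustment to the other two models.
- **The covariate list is open.** Gender, age and disease course are examples. A reader might infer that baseline EASI has been ruled out; the wording does not say so. This stands, but adding baseline EASI to the list would not make either model fit.
- **Detail is deferred to an SAP and the subtrial protocols.** Those may well name a linear model. The article nonetheless names its models, and they do not fit its first primary outcome. This is a stated mismatch, not silence.
- **The planned test is valid.** A reader might infer bias or a raised false-positive rate. Neither follows: the unadjusted comparison is unbiased under randomisation and, if anything, slightly conservative under centre stratification. This stands.
- **No power figure comes from the article.** Rho, the SD ratio and the 80% are all assumed. Table 2 limits CHARM to BSA between 1% and 10% and IGA 1 to 3, which may compress baseline spread and shrink the gain. This stands, so a particular loss of power cannot be claimed as established.

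**Conclusion.** The concern holds for continuous outcomes, and it matters most for the CHARM primary outcome. As written, its main test is unadjusted and the stated adjustment for centre and other factors cannot be fitted.

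The step 3 figures put the loss at about 14 percentage points of power at rho 0.3, falling to 2 at rho 0.9. They assume equal SDs and 80% power for the unadjusted test; unequal SDs move the loss in either direction.

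Because the planned test remains valid and the loss is of unknown size, this is a should-fix point. The documents do not support treating it as a threat to the trial's validity.

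**What to change.** In section 2.8.2, and in the SAP before unblinding:

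1. Analyse EASI change (or week-4 EASI) with a linear model, either ANCOVA or a mixed model for repeated measures, on treatment, baseline EASI and centre. Report the adjusted mean difference with its 95% CI.
2. Keep the t-test or Mann–Whitney test for EASI as supportive.
3. Use linear models for adjusted analyses of the other continuous outcomes.
4. Keep logistic regression with centre for binary outcomes, including adequate-relief response.
5. Remove Cox regression from the RCT analysis unless a time-to-event outcome is defined.

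The cost is a change of wording. Baseline EASI and centre are already recorded, and no further data or patients are needed.

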### 2.2. Study Design and Setting

This master protocol consists of two multicenter, double-blinded, randomized placebo-controlled trials and a real-world observational study (Table 1): the CHARM trial (the Chinese herbal formula Huoxiang Zhengqi for atopic dermatitis with dampness pattern) [25] and the CHAIRS trial (the Chinese herbal formula Huoxiang Zhengqi for diarrhea-predominant irritable bowel syndrome) [26]. At the beginning of this trial, two registry-based cohorts of AD and IBS-D will be established, where patients with dampness pattern will be enrolled in the RCTs, and patients with nondampness pattern will be retained in the cohort constituting a real-world observational study. Thus, dampness pattern will be contrasted with nondampness pattern.

A total of 678 AD patients and 322 IBS-D patients will be enrolled from 14 hospitals in China over a 3-year period. Patients in the RCTs will be randomized at a ratio of 1 : 1 to receive either HXZQ oral liquid or a placebo for 4 weeks and then be followed up for another 4 weeks, while patients in the observational study will experience a 12-week follow-up.  Figure 1 displays the study flowchart. This study has been approved by the Ethics Committees of each participating site. Substudies have been registered in the Chinese Clinical Trial Registry (ChiCTR1900026700 and ChiCTR1900026837). An independent data safety monitoring board (DSMB) will monitor the overall conduct of the trial and assess the safety and efficacy of study procedures.

CHARM, Chinese herbal formula Huoxiang Zhengqi for atopic dermatitis with dampness pattern; CHAIRS, Chinese herbal formula Huoxiang Zhengqi for diarrhea-predominant irritable bowel syndrome; AD, atopic dermatitis; IBS-D, diarrhea-predominant irritable bowel syndrome; HXZQ, Huoxiang Zhengqi oral liquid.

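### CHARM's continuous primary outcome is compared by an unadjusted test, and the only adjustment models named for the RCTs, logistic and Cox, cannot be fitted to it

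*Protocol article*

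**What the plan says.** Section 2.5.1 of the protocol article states for AD patients that "the primary outcome is the change in the Eczema Area and Severity Index (EASI) scores from baseline to the end of treatment", at week 4. This is a continuous outcome. Table 3 schedules EASI at baseline and at weeks 2, 4 and 8 in the RCTs.

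Section 2.8.2 sets the between-group comparison for all outcomes: a t-test or Mann–Whitney U test for continuous variables ("test will be employed for continuous variables") and a chi-squared or Fisher's exact test for categorical ones. It adds that "The changes across time among outcomes will be analyzed by repeated measure analysis of variance", with no covariates stated. The only adjustment sentence for the RCTs then says that centre effect and other factors chosen on professional judgement, such as "gender, age, and disease course will be adjusted by logistic regression model or Cox regression model".

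Section 2.4.3 makes centre the stratification factor: "A center-stratified random sequence will be created with SAS 9.2". Allocation is 1:1 (section 2.2), and two-sided P "values <0.05 are considered statistically significant" (section 2.8.2).

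**The concern.** Logistic regression needs a categorical outcome and Cox regression a time to event. EASI change is neither, and section 2.5 defines no time-to-event outcome. The article thus says that centre will be adjusted for and names models that cannot do it for CHARM's primary outcome. The same misfit affects the other continuous outcomes: pruritus NRS, BSA, Skindex-29 and EQ-5D-5L in AD, and IBS-SSS, IBS-QOL and EQ-5D-5L in IBS-D.

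Precision is at stake. A change score analysed without baseline as a covariate carries baseline noise that a linear model would remove, and a test that ignores the stratifier has a standard error that is somewhat too wide. An analysis plan that followed the sentence literally would inherit a model that cannot be run.

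**Working it through.** **1. The plan's own figure.** CHARM randomises 218 patients, 109 per arm. This number cannot be reproduced: section 2.8.1 gives no EASI difference, SD or power and refers to the subtrial protocols. The results below are therefore relative to an assumed starting power.

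**2. Does another sentence supply a usable model?** Repeated measures ANOVA (section 2.8.2) concerns change across time and has no stated covariates, centre term or week-4 contrast. The mixed-effects or multilevel models in the overall-analysis part of section 2.8.2 are for the process of CM pattern change, not EASI. The logistic, Cox and Bayesian hierarchical models there are for a prognosis model. None gives a covariate-adjusted comparison of EASI change.

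**3. Variance ratio.** Set the baseline SD to 1, the week-4 SD to s and their correlation to rho.
- Variance of the change score: 1 + s² − 2·rho·s
- Residual variance under ANCOVA: s²(1 − rho²)
- Ratio R = (1 + s² − 2·rho·s) / [s²(1 − rho²)]
- With s = 1, R = 2(1 − rho)/(1 − rho²) = 2/(1 + rho)

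**4. Power.** Take 80% power for the change-score t-test at two-sided 0.05, so z-values sum to 1.960 + 0.8416 = 2.8016. With 109 per arm this is a standardised difference of 2.8016 × √(2/109) = 0.379. ANCOVA power = Φ(2.8016·√R − 1.96). The total N giving ANCOVA the same 80% power is 218/R, rounded up to an even number. The documents give neither rho nor s, so both are assumed.

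| rho (s = 1) | R | ANCOVA power | Total N for 80% |
|---|---|---|---|
| 0.3 | 1.54 | 93.5% | 142 |
| 0.5 | 1.33 | 89.9% | 164 |
| 0.7 | 1.18 | 86.0% | 186 |
| 0.9 | 1.05 | 82.0% | 208 |

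Starting from 90% power (standardised difference 0.439), the ANCOVA figures are 98.0%, 96.3%, 94.0% and 91.4%.

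**5. Unequal SDs, from an 80% base.**
- s = 1.2, rho = 0.5: R = 1.24/1.08 = 1.148, power about 85%.
- s = 1.2, rho = 0.7: R = 0.76/0.7344 = 1.035, power about 81%.
- s = 0.8, rho = 0.5: R = 0.84/0.48 = 1.75, power about 96%.
- s = 0.8, rho = 0.7: R = 0.52/0.3264 = 1.593, power about 94%.

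**6. Centre.** Let centre explain a share c of the outcome variance (assumed). A test that ignores a balanced stratifier has a true two-sided error of about 2[1 − Φ(1.96/√(1 − c))].
- c = 5%: about 0.044. Adjusting for centre alone lifts 80% power to 82%.
- c = 10%: about 0.039. Adjusting for centre alone lifts 80% power to 84%.

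The unadjusted test errs on the conservative side. With baseline EASI and c = 10% together (s = 1), power is 92.6% at rho 0.5 and 89.3% at rho 0.7.

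**The case against.** The best defence is that this article condenses a master protocol, cites the subtrial protocols for each RCT's analysis and announces a later SAP. The covariate set, the rule for choosing between t-test and Mann–Whitney, and the handling of small centres usually belong there. That stands, and silence on those details is not the point. The article is not silent on the adjustment model, however. It names two, and neither fits the primary outcome of one of its two trials.

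Four stronger readings are tempting, and the documents do not support them.
- A reader might infer that baseline EASI and centre play no part in the analysis. Baseline enters the change score by subtraction and could be a time point in the repeated measures ANOVA. The list of factors is open-ended, and the text does intend a centre adjustment. The fault lies in the models named.
- A reader might infer that the primary test is biased. Under 1:1 randomisation a t-test on change is valid, and ignoring the stratifier makes it conservative.
- A reader might infer that CHARM is underpowered. The inputs behind 218 are not in the article, so no shortfall against planned power can be shown.
- A reader might infer that the adjustment sentence fails throughout. Logistic regression fits AR response, EASI-50 and EASI-75, so it suits the primary outcome of CHAIRS.

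It is also fair to say that the gain from ANCOVA may be small. CHARM restricts baseline severity (BSA above 1% and below 10%, IGA 1 to 3), which could leave the week-4 SD larger than the baseline SD. The s = 1.2 cases cover this.

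**Conclusion.** The point holds as a mismatch in stated text, and it should be fixed. Section 2.8.2 compares CHARM's continuous primary outcome without adjustment and offers only adjustment models that cannot take it. The stated centre adjustment cannot be carried out for that outcome as written, and baseline EASI is not named as a covariate although it is collected.

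The consequence is efficiency forgone by a valid test. From an assumed 80% base with equal SDs, ANCOVA on baseline EASI adds about 2 points (rho 0.9) to 14 points (rho 0.3). With an SD ratio of 1.2 the gain falls to about 5 points at rho 0.5 and 1 point at rho 0.7. These figures rest on assumed correlations, SD ratios and starting power. The misfit of the named models to a continuous outcome rests on no assumption.

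**What to change.** - **Primary CHARM analysis:** one linear model (ANCOVA) of EASI change to week 4 on treatment, baseline EASI and centre, with small centres pooled or centre as a random effect. Report the adjusted mean difference with its 95% CI.
- **Other continuous outcomes in both RCTs:** the same form, each with its own baseline value.
- **t-test or Mann–Whitney:** keep as supportive analyses.
- **Logistic regression:** limit to binary outcomes (AR response, EASI-50, EASI-75).
- **Cox regression:** limit to any outcome that is defined as a time to event.

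The cost is wording in the protocol and SAP, best settled before unblinding. Baseline EASI and centre are already recorded, so no added patients, visits or measurements are needed.

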#### 2.4.2. Concomitant Medications

For AD patients in the RCT, topical daily use of moisturizers such as urea ointment is recommended and permitted. Cetirizine hydrochloride tablets will be used in case of intolerable itching, and the dosage and frequency should be recorded. Other effective medications (orally or externally) and phototherapy for AD are not allowed. For IBS-D patients enrolled in the RCT, intolerable abdominal pain or diarrhea can be treated with emergency medications prescribed by the clinician. The name and dosage of the medication should be recorded in the patient's diary. Besides, any other medications and CM physiotherapy (such as acupuncture, moxibustion, or cupping) that may be effective for IBS-D, or can relieve abdominal pain and diarrhea, are prohibited. Treatments in the observational study will be provided by clinicians according to patients' specific conditions, and medical records of each patient should be exactly documented.

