### 2.6. Safety Assessment

Adverse events (AEs) will be reported to the investigators following the ICH-E2A guideline [31], and the causality between AEs and interventions will be assessed according to the WHO-UMC System for Standardized Case Causality Assessment [32]. Any event classified as “severe” or “life-threatening” in severity is considered a serious AE (SAE) and must be reported to the research ethics committee within 24 hours. Safety laboratory tests (routine blood, routine urinalysis, biochemical indexes of liver, and renal function) and electrocardiogram examination will be regularly conducted at baseline and 4^th^ week in the RCTs. Abnormal changes in laboratory examination will be judged by clinicians whether they have clinical importance and can be considered an AE. Safety assessment in the observational study will follow the guidance of clinicians.

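### Adverse events in the observational study are sent to the unadjusted RCT tests while its outcomes are propensity-matched, so any AE comparison between medication groups made that way is open to confounding by indication

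*Protocol article*

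**What the plan says.** Four statements in the protocol article bear on this.

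- **How treatment is assigned (section 2.4.2).** "Treatments in the observational study will be provided by clinicians according to patients' specific conditions". Section 2.4.3 adds: "In the observational study part, patients will receive no experimental interventions of this study".
- **How the observational outcomes are compared (section 2.8.2).** The comparison is between medication groups, by propensity score matching.
- **How observational safety is handled (section 2.8.2, two sentences that follow one another).** Directly after the matching sentence comes "Safety assessments of observational part will follow the same procedures and methods as those in the RCTs". Section 2.6 says something different: "Safety assessment in the observational study will follow the guidance of clinicians".
- **What the RCT safety method is (section 2.8.2).** "comparisons of the incidence and severity of AEs or adverse drug reactions (ADRs) between the groups will be performed by Chi-square test", with the list continuing "Fisher's exact test, or Wilcoxon rank-sum tests based on the data characteristics". A summary table of AEs is added. An earlier sentence in the same paragraph provides logistic or Cox regression to adjust for centre and patient factors, but it is not linked to safety.

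**The concern.** In the RCTs an unadjusted comparison of AE counts is sound because randomisation balances the arms on average. The observational study has no such protection. If patients with worse disease tend to get certain medicines and also tend to report more AEs, an unadjusted test picks up who received each medicine as well as what the medicine did. It can produce a false safety signal or hide a real one.

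The plan already accepts this for outcomes, since it matches the medication groups before comparing them. The same reasoning applies to AEs in those patients, yet the safety sentence points to a method built for randomised groups. This is an instruction in the text and not merely a detail left to the statistical analysis plan: an analysis plan that followed it literally would carry the problem forward.

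**Working it through.** **1. Does the matching sentence already cover AEs?** It refers to all outcomes. The article keeps safety apart from outcomes throughout:

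- outcomes are in section 2.5 and safety is in section 2.6;
- Table 3 has one block for outcome measurements and another for safety assessment;
- the RCT paragraph of section 2.8.2 gives tests for all outcomes and then gives safety tests separately.

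On that usage, all outcomes does not plainly include AEs, and safety then gets its own sentence.

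**2. Does any adjustment reach AEs by another route?** The logistic/Cox sentence comes before the safety sentence and is not tied to it. Section 2.6 names no analysis method for the observational part. So no sentence extends matching or adjustment to AEs.

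**3. How large could the effect be?** The plan states no figure on this point, so there is none to reproduce. The following is an illustration.

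*From the article:* 460 AD and 110 IBS-D patients in the observational study (Table 1); two-sided 5% significance (section 2.8.2).

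*Assumed:* two medication groups A and B of equal size; no drug effect on AEs; one yes/no severity factor. A share s of each group is severe. AE risk is r1 in severe patients and r0 in milder ones.

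Expected AE rate in a group: s × r1 + (1 − s) × r0.
Spurious difference between groups: (sA − sB) × (r1 − r0).

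Example with sA = 0.7, sB = 0.3, r1 = 0.15, r0 = 0.05:

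- Group A: 0.7 × 0.15 + 0.3 × 0.05 = 0.12
- Group B: 0.3 × 0.15 + 0.7 × 0.05 = 0.08
- Difference 0.04, ratio 1.50, with no drug effect at all
- With 230 per group, SE = √[(0.12 × 0.88 + 0.08 × 0.92)/230] = 0.0279, so 0.04/0.0279 = 1.43
- Chance of P < 0.05 ≈ Φ(1.43 − 1.96) ≈ 0.30

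Simulation, 20,000 studies per row and sample size. The adjusted column is a Mantel-Haenszel test stratified on severity, standing in for a matched or adjusted analysis.

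| Severe, A vs B | AE risk, severe vs milder | AE rate, A vs B | Ratio | Crude, N = 460 | Crude, N = 110 | Adjusted, N = 460 / 110 |
|---|---|---|---|---|---|---|
| 50% vs 50% | 15% vs 5% | 10% vs 10% | 1.00 | 0.050 | 0.050 | 0.049 / 0.049 |
| 60% vs 40% | 10% vs 5% | 8% vs 7% | 1.14 | 0.069 | 0.051 | 0.051 / 0.049 |
| 60% vs 40% | 15% vs 5% | 11% vs 9% | 1.22 | 0.106 | 0.065 | 0.048 / 0.047 |
| 60% vs 40% | 30% vs 10% | 22% vs 18% | 1.22 | 0.191 | 0.081 | 0.052 / 0.048 |
| 70% vs 30% | 10% vs 5% | 8.5% vs 6.5% | 1.31 | 0.127 | 0.064 | 0.051 / 0.047 |
| 70% vs 30% | 15% vs 5% | 12% vs 8% | 1.50 | 0.305 | 0.103 | 0.050 / 0.048 |
| 70% vs 30% | 30% vs 10% | 24% vs 16% | 1.50 | 0.576 | 0.183 | 0.048 / 0.049 |

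The first row is the situation in an RCT: with case mix balanced, the crude test holds its 5% level. The adjusted column assumes that the confounder is measured; matching cannot remove imbalance in a factor that was not recorded.

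**The case against.** The strongest reply is that the article never says observational AEs will be compared unmatched. Matching builds comparable sets and is not itself a test. A Chi-square, Fisher or Wilcoxon test could still be run inside the matched sets, and the reference to RCT methods may name only the tests. This stands in part: the text does not forbid it. It does not say it either, and it defines the safety method by pointing to trials that have no matched sets.

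Second, the safety sentence names no comparison groups. In the RCT paragraph the groups are HXZQ and placebo, which have no counterpart as study arms here. That the comparison would be between medication groups is inferred from the preceding sentence. This stands, and the point is therefore conditional on such a comparison being made.

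Third, the sentence is loose shorthand. Table 3 schedules laboratory tests and ECG at baseline and week 4 in the RCTs but only at baseline in the observational study, and section 2.6 leaves observational safety to clinicians. This also stands. It argues for rewording the sentence and does not show that AEs are matched.

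Fourth, this is a condensed article with an analysis plan to follow, and the comparative safety of clinician-chosen treatments is a side question to the HXZQ objective in section 2.1. That lowers the weight. It does not turn a stated rule into an omission.

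A reader might go further and infer that observational safety results will be confounded, or that effectiveness and safety are bound to be reported in two different populations so that benefit and risk cannot be read together. The documents support neither. The first needs case-mix and AE-risk figures that they do not give. The second needs an unmatched analysis that they do not specify.

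**Conclusion.** The point holds in conditional form. Read literally, the plan applies tests that rely on randomisation to AEs in patients whose treatment was chosen by their clinicians, while it matches the outcomes of those patients. Any AE comparison between medication groups made that way is open to confounding by indication.

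Its size is unknown. Across the unbalanced scenarios the crude false-positive rate was 7% to 58% in AD and 5% to 18% in IBS-D, against 5% nominal. These ranges rest wholly on assumed severity splits, assumed AE risks, two equal groups and no loss to follow-up. They show that the problem can range from negligible to serious, and they do not predict what this study will find.

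Severity is minor to moderate. The randomised HXZQ safety comparison is unaffected, HXZQ is not a study intervention in this part, and the observational effectiveness analysis is called exploratory.

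**What to change.** Replace the safety sentence in the observational paragraph of section 2.8.2 with wording such as:

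*AE and ADR incidence and severity in the observational study will be compared between medication groups in the same propensity-score-matched sets as the other outcomes, or with a propensity-adjusted model. AE rates in all observational patients will be tabulated descriptively, without P values.*

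If no comparison between medication groups is intended for safety, the descriptive sentence alone is enough. In the same edit, reconcile section 2.8.2 with section 2.6, so that one statement governs how observational safety is collected and another how it is analysed.

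The cost is one or two sentences now, plus AE tables run on matched sets that will already exist. The downside of matching is that unmatched patients leave the comparison, which matters most for uncommon events. They stay in the descriptive tables, and the adjusted model is the alternative if that loss is too great.
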